## Abstract

**Background:**

Prevention of alcohol, drug and tobacco misuse by young people is a key public health priority. There is a need to develop the evidence base through rigorous evaluations of innovative approaches to substance misuse prevention. The Strengthening Families Programme 10–14 is a universal family-based alcohol, drugs and tobacco prevention programme, which has achieved promising results in US trials, and which now requires cross-cultural assessment. This paper therefore describes the protocol for a randomised controlled trial of the UK version of the Strengthening Families Programme 10–14 (SFP 10–14 UK).

**Methods/Design:**

The trial comprises a pragmatic cluster randomised controlled effectiveness trial with families as the unit of randomisation, with embedded process and economic evaluations. Participating families will be randomised to one of two treatment groups - usual care with full access to existing services (control group), or usual care plus SFP 10–14 UK (intervention group). The trial has two primary outcomes - the number of occasions that young people report having drunk alcohol in the last 30 days, and drunkenness during the last 30 days, both dichotomised as ‘never’ and ‘1-2 times or more’. The main follow-up is at 2 years past baseline, and short-term and intermediate outcomes are also measured at 9 and 15 months.

**Discussion:**

The results from this trial will provide evidence on the effectiveness and cost-effectiveness of an innovative universal family-based substance misuse prevention programme in a UK context.

**Trial registration:**

Current Controlled Trials ISRCTN63550893.

## Background

Risk behaviour by young people, including substance misuse (alcohol, tobacco and illegal drugs), antisocial behaviour and crime has a substantial impact on the UK economy and the health of its population. These behaviours are associated with morbidity and mortality among young people, poor education, social exclusion, teenage pregnancy, conduct disorders and poor health over the life course
[1-3]. The 2009/10 HBSC survey in Wales indicated that at age 15, 50% of girls and 47% of boys reported that they had been drunk twice or more (the third highest of 38 countries); 16% of girls and 11% of boys reported that they smoked cigarettes at least once a week; and 20% of girls and 22% of boys reported that they had ever used cannabis. Concerning drunkenness and cannabis use prevalence, Wales, Scotland and England all had rates above the HBSC average
[4].

Intervention efforts have largely focussed on individual risk behaviours, ignoring the co-occurrence of multiple health risk behaviours
[5]. In the 2012 survey of drug use, smoking and drinking among 11–15 year olds in England, 6% of respondents had smoked during the last week (rising to 15% by age 15)
[6]. Past week smoking was strongly associated with other risk behaviours, and “[o]f the 6% of pupils who reported smoking in the last week, most (5% of all pupils) had also drunk alcohol or taken drugs recently, or had done both” (p185).

The survey also found that truanting from school was linked to these behaviours. For instance, “[p]upils who had truanted from school were more likely to be regular smokers compared with pupils who had never truanted (odds ratio = 2.02)” (p36).

Understanding the co-occurrence of multiple health risk behaviours and their association with poor educational outcomes, social disadvantage, conduct disorders and poor physical and emotional health is therefore an important area of current public health research
[5,7-10]. Similarly, there is increased interest in prevention efforts which focus on risk and protective factors such as pro-social behaviour, resilience and positive youth development
[11-13], and which therefore have the potential to impact upon multiple risk outcomes. Family-based risk and protective factors have been identified as important targets for intervention
[14], including the modelling of parents’ alcohol use
[15], rules and monitoring around substance use
[16,17], and more general parenting styles and relationships within families
[18-20]. Parenting and family interventions form a central part of many governments’ health, welfare and education policies, and prevention of substance misuse is also a key priority
[21-25]. Yet interventions are often developed without reference to the existing evidence base or theoretical frameworks, and implemented without rigorous evaluation
[26].

A promising programme which has targeted multiple risk behaviours by addressing risk and protective factors located in the family is the Strengthening Families Programme 10–14 (SFP 10–14). It draws on theories of bio-psychosocial vulnerability, resiliency and family process, and was initially developed as the 14-session Strengthening Families Programme for high-risk families with children aged 6–12 years whose parents were misusing alcohol or drugs. The revised SFP 10–14 is a seven week universal programme targeting young people aged 10 to 14 years and their parents
[27]. SFP 10–14 has been reported to be effective over a six-year follow-up period in promoting family integration, delaying the onset of alcohol use, reducing uptake of smoking, the incidence of harder drug use (methamphetamine)
[28-31] and substance use at 10 year follow-up (aged 21)
[32]. Delaying the age of initiation of substance use is an important goal, since epidemiological research has indicated that later onset of alcohol and drug use is associated with reduced lifetime prevalence of alcohol and drug problems
[33-35].

US-based cost-benefit assessments indicate that SFP 10–14 can be cost-effective at the population level for preventing alcohol misuse, other alcohol problems and also for tobacco use
[36-38], cannabis and other drug use prevention. A potential ten-fold return for every dollar invested in the programme has been reported
[36], although the authors conclude that economic analysis had largely been unexplored in the evaluation of such interventions. Another US study that examined the SFP 10–14 alongside other school-based programmes has shown that the costs of participation amounted to US$150 while the benefits realised could be as much as US$1000 per participant, depending on the extent of drug use
[38]. The emphasis in these studies has been on the cost-benefit ratio and whether prevention can generate returns on investment from avoidance of other costs in other sectors and in future years. The results of such studies are highly dependent on the perspective taken and the nature and range of assumptions made. Most critically, they are dependent on the existence of high quality investigations that utilise reliable and valid outcome measures to produce indications of effect and that yield detailed and relevant cost information from a range of perspectives. Well conducted studies of this nature can contribute to subsequent meta-analyses and modelling exercises to identify efficient policy options.

The current evidence base for SFP 10–14 is derived exclusively from the US from two trials conducted by the same research team. Recent Cochrane systematic reviews and a 2006 technical report to the *World Health Organisation (WHO) Expert Committee on Problems Related to Alcohol Consumption* recommend that the SFP 10–14 is adapted and tested in other cultures and settings before widespread implementation
[39,40]. Recent methodological critiques of the two existing RCTs of SFP 10–14 point to limitations in the statistical analyses by the original research team, namely the use of multiple and one sided statistical tests leading to claims of statistical significance at p < 0.05 that may not be justified
[41-45]. In these critiques the key issue is statistical precision, and an intention-to-treat re-analysis of the original data for a Cochrane review highlighted that the results of the SFP 10–14 trials showed an important effect with low precision
[39]. For example, in this re-analysis the Absolute Risk Reduction and 95% confidence interval for drunkenness was 11.27% (0.31% to 22.24%). This underlines the need for additional, high quality trials to assess effectiveness and cost-effectiveness with precision and determine whether the programme has long-term public health benefits. This view is reinforced by a recent independent UK Department of Health-commissioned review of prevention and behaviour change in young people, which concluded that “More RCTs [are needed] of the Strengthening Families Program”
[46].

It is not clear whether the apparent effectiveness of the SFP 10–14 in reducing alcohol and drug problems at the population level, as shown in research from the United States, will translate to other cultures, settings and countries. The SFP 10–14 has recently been culturally adapted for use in the UK
[47,48] and there is substantial UK policy interest in the programme. This includes the use of the SFP 10–14 as part of the UK Government’s Family Intervention Projects across a small number of selected sites in England, which target high risk families
[49]. An evaluation of the programme’s implementation in Barnsley, England (which mainly used the original US programme materials), highlighted the need for some cultural adaptation (now completed) and consideration of the best approach with regards to universal or high-risk targeting
[50,51]. Many studies have highlighted the challenges associated with targeted programmes for young people, including recruitment, stigmatisation, and managing group dynamics, with the potential for harmful peer modelling effects
[52-58]. Such targeting also risks losing the beneficial group effects which are achieved through the universal delivery of programmes such as SFP 10–14 to whole school populations, as in the US SFP10-14. In Cardiff, Wales, UK, these problems led to the development of an innovative approach of providing the SFP 10–14 as a universal intervention (available to any family via practitioner referral or family application), and running mixed groups of families from the ‘general population’ in combination with families with challenges (in the context of a group setting)
[59], with the aim of promoting positive group dynamics. Groups of families attending the SFP therefore normally comprise around 70% from the general population, and 30% who may experience or present challenges in a group setting (families with challenges). It should be noted that in this ‘mixed families’ approach, such challenges relate specifically to the delivery and receipt of the group sessions, rather than general characteristics of participants’ support needs, family functioning or other risk factors. Examples of the challenges experienced or presented by families therefore include issues such as low literacy levels, behavioural problems (e.g. anger/aggression) and exclusion of children from school (and who may find working in a group setting challenging). An earlier paper describes the mixed families approach in more detail
[59]. These mixed groups demonstrated evidence of high levels of participant retention and acceptability, and social effects outside the programme, with participating families supporting each other between sessions and after the end of the programme. Our trial of the SFP 10–14 UK in Wales (Project SFP Cymru) uses this ‘mixed families’ approach to group recruitment and composition, as well as the fully culturally adapted materials. The trial therefore builds on the completed formative evaluation, adaptation and exploratory evaluation of the UK version of the programme
[47,48,50,51,59], and will generate important new evidence on the programme’s long-term effectiveness and cost-effectiveness in the UK.

## Methods/design

### Study design

The trial comprises a pragmatic cluster randomised controlled effectiveness trial with families as the unit of randomisation, with embedded process and economic evaluations.

### Recruitment

SFP 10–14 UK will be implemented in seven geographical areas of Wales by local agencies that are independent of the research team (e.g. local authority parenting teams, children’s charities). Trial areas will run the programme on approximately 8 occasions over a two year period, with a maximum capacity of 10–12 intervention families per programme.

SFP 10–14 UK is designed for delivery to families with children aged 10–14, and in the Wales adaptation is targeted towards a mix of children and their families. Each programme is open to families from a loosely defined and fairly large geographical area. In each area, self-referrals to the Programme come forward in response to awareness-raising in community and educational settings. Other referrals come from agencies such as education, health and social services which identify families that may benefit from participating in the Programme.

Potential referrers and families are informed that the Programme is being run as part of a trial and are provided with brief information about the trial. When a family is referred or applies to the SFP 10–14 they will be visited by a member of the programme delivery team (normally the programme coordinator) who will undertake a needs and eligibility assessment. Based on the information contained in the family referral/application form and the needs and eligibility assessment the coordinator determines if eligible families are from the ‘general population’ or a family with challenges (in the context of a group setting). If families are deemed eligible to attend the programme they will be asked if they are willing for a member of the research team to have access to their referral notes and to visit them. Where the family agrees a research fieldworker will then visit them to obtain informed consent to participate in the trial, collect baseline data using a computer assisted personal interview (CAPI), and inform the family of the treatment group (C or I) to which they have been randomised. Figure 
1 shows the anticipated flow of participants through the trial.

**Figure 1 F1:**
[figure not shown]
Participant flow diagram.

We will offer all parents and young people who provide data at 2 year follow-up a £10 gift voucher. All adults who take part in the 9 and/or 15 month interviews will be entered in to a prize draw with the chance to win a £50 family outing. Adults have a 1 in 20 chance of winning.

### Participants

#### Inclusion and exclusion criteria

Table 
1 describes the trial’s inclusion and exclusion criteria. Any families deemed eligible to attend SFP 10–14 UK will be included in the research trial, subject to their giving consent. Only families agreeing to participate in the trial and randomised to receive the intervention will have access to SFP 10–14 UK.

**Table 1 T1:** Trial inclusion and exclusion criteria

**Inclusion criteria**	**Exclusion criteria**
At least one parent/carer and one child are willing to attend the programme together	Situations where either a parent or child does not want to attend the programme
The ability to speak English (help can be provided for parents or children with low literacy levels). Some programmes may also be delivered through the medium of Welsh if there is sufficient demand	Parents or children who cannot speak English (or Welsh, where appropriate)
A programme is being offered at a location to which it is practicable for a family to travel (as determined by the programme coordinator) within the next three months	No programme is being offered at a location to which it is practicable for a family to travel (as determined by the programme coordinator) within the next three months. In such a case the family would not be excluded. They will be placed on a waiting list for the programme and will be contacted when a programme is available. They will then be recruited into the trial
Families with a child aged 10-14	-
-	Families who do not live together - e.g. the child/children are in care
-	Families with very high needs or challenges (such as serious substance misuse problems, family breakdown or crisis)

### Ethical approval

Ethical approval for the trial was given by the Research Ethics Committee for Wales (reference 09/MRE09/53).

### Informed consent

Prior to being visited by a research fieldworker, all families who are invited to participate in the research trial will be mailed an information sheet. This will include specific documents for parents/carers and young people. There will also be information for parents/carers about our request to involve their children in the trial. The fieldworker will go through this information with families and address any queries or concerns that they may have.

Informed consent will be obtained from all participants. For a family to be included in the research trial at least one parent/carer must consent to participate, and parent/carer consent for the inclusion of at least one young person in the trial is required. Young people will also need to give consent for their participation in the research trial. The fieldworker will be careful not to offer, or in any way imply access to the programme.

### Randomisation

Families agreeing to participate in the research trial and who provide baseline data will be randomised using a computerised randomisation facility that will randomise families within strata defined by area (7) and use minimisation on the following variables:

• the category to which the family have been assigned (general population/family with challenges);

• age of children wishing to attend the programme (<12/12+). A mean will be taken if there is more than one child; and

• the number of children in the family wishing to attend the programme (1/>1).

There will be complete concealment of the randomisation sequence, set up securely within the randomisation database by the statistician, from the field recruitment staff and other trial team members. A random element, set at 80%, will also be used to increase the integrity and reduce the deterministic nature of the randomisation process.

### Intervention

Participating families will be randomised to one of two treatment groups. Either they will receive usual care with full access to existing services and a minimal information leaflet (control group-C), or they will receive the SFP 10–14 UK programme in addition to usual care with full access to existing services (intervention group – I). There will not be a defined programme of usual care, and the existing variation in services available to participants across the participating areas will continue throughout the trial period.

SFP 10–14 is open to families from a loosely defined and fairly large geographical area. The ‘mixed families’ approach aims to recruit about 4 families with challenges per group, and 6–8 families from the ‘general population’. Self-referrals (applications by families) come forward from awareness-raising in community and educational settings. Families are therefore drawn from the same area facilitating mutual support between sessions and at the end of the programme, but are not normally from a small or defined community such as a school or local neighbourhood. The programme comprises seven weekly sessions of two hours and is delivered in a range of community venues by a multi-agency team of trained professionals. In each session there is an hour during which parent sessions and young people sessions are conducted separately, followed by a second combined family hour. Typically the first hour focuses on skills (e.g. peer resistance for the young people, parenting for the parents), with the second hour designed to enable parents and young people to focus on communication skills, recognise family strengths, and practice skills covered in the first hour
[27].

### Objectives

The trial’s primary objective is to assess the effectiveness of the SFP 10–14 UK in preventing alcohol misuse in young people. Its secondary objectives are to assess the programme’s impact on drug misuse, smoking behaviour, alcohol initiation and drink-related problems and school performance, among young people. Tertiary objectives are to measure the extent to which SFP 10–14 UK has effects on mental health and wellbeing, and protective factors for alcohol and tobacco use/misuse located in the family (e.g. family functioning, parenting and young people’s peer resistance skills). The trial will measure the costs associated with programme delivery and whether it is cost effective. It will assess if there are important variations in delivery and receipt across trial sites, and identify key programme theory, content and processes.

### Outcome measures

The trial has two **primary outcomes** - the number of occasions that young people report having drunk alcohol in the last 30 days; and drunkenness during the last 30 days, dichotomised as ‘never’ and ‘1-2 times or more’. **Secondary outcomes** (mainly concerned with long-term alcohol/tobacco/substance behaviours) are: reported use of cannabis (ever vs. never); weekly smoking (yes vs no, validated by salivary cotinine measures); age of alcohol use initiation; frequency of drinking more than 5 drinks in a row in the last 30 days; frequency of different types of alcoholic drinks; alcohol-related problems; and General Certificate of Secondary Education (GCSE) performance at age 15/16 (number of GCSEs passed and grades achieved, measured as a continuous outcome). All primary and secondary outcomes are collected from children at 2 year follow-up, with the exception of GCSE results, which we propose to collect via the Secure Anonymised Information Linkage (SAIL) Databank
[60], once all participants have completed GCSEs/left compulsory education. The trial’s **tertiary outcomes** (mainly concerned with health and family wellbeing, and also substance use initiation) are: parenting (General Child Management Scale child report); family functioning (Family Relationship Index); children’s wellbeing and stress (Strengths and Difficulties Questionnaire scores); children’s health status (SF-36); parents/carers’ health status (GHQ and EQ5D); indicators of relative cost-effectiveness (derived from the health data); children’s smoking status (i.e. whether they have ever smoked/smoke now); young people’s self-efficacy; age of first cigarette; and age of first drug use. Tables 
2,
3,
4,
5, and
6 provide a description of the trial’s primary, secondary and tertiary outcomes, and the specific measures used in each of the data collections. Selection of outcomes at 9, 15 and 24 months was informed by a literature review undertaken as part of the process evaluation.

**Table 2 T2:** Measures collected at baseline from young people

**Domain/question topic**	**Purpose**	**Measure/source**

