### Sample size

We will aim to recruit 378 families in each arm of the trial (756 families in total). This will provide us with at least 80% power at the 2.5% level (halved to account for our two primary outcomes) to detect either a 12% difference in young people reporting having drunk alcohol (assuming a control group prevalence of 48%
[4]), or a 10% difference in young people reporting having been drunk (assuming a prevalence of 22%
[4]), at two year follow-up. This sample size is based on an average family in the trial having 1.25 young people, an intracluster correlation coefficient (ICC) of 0.2 and is adjusted to allow for 25% loss to follow-up (including withdrawals from the trial by participants prior to 24 month follow-up).

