Educational achievement at 16 will be compared between trial arms by fitting a two-level logistic regression model (young people nested within families) comparing the proportion of young people who obtain five or more GCSEs at a grade C or above (GCSE Grades use an A*-G scale, with A* being the highest score). The proportion of young people who continue in education beyond 16 will be similarly compared between trial arms by fitting a logistic regression model. This analysis will be performed on the whole sample following the date that all participants (young people) should have completed school Year 11 when GCSEs are normally awarded. Other secondary and tertiary outcomes (e.g. parenting and child management, parent–child affective behaviour and wellbeing and stress) will be analysed by fitting similar regression models, controlling for clustering of responses within families (as appropriate) and controlling for variables that were balanced on at randomisation.

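### GCSE performance is declared as a continuous secondary outcome, but the only attainment analysis stated is a logistic model of a pass threshold

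*Protocol article*

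**What the plan says.** Three places in the protocol article bear on this.

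- **Outcome measures** lists GCSE performance at age 15/16 among the secondary outcomes and fixes its scale: "number of GCSEs passed and grades achieved, measured as a continuous outcome". The results are to come by record linkage after all participants have passed the end of compulsory schooling.
- **Main analysis** gives the model: "Educational achievement at 16 will be compared between trial arms by fitting a two-level logistic regression model", and the quantity compared: "comparing the proportion of young people who obtain five or more GCSEs at a grade C or above". On timing it adds: "This analysis will be performed on the whole sample following the date that all participants (young people) should have completed school Year 11".
- **Main analysis** closes its secondary part with a general provision: "Other secondary and tertiary outcomes (e.g. parenting and child management, parent–child affective behaviour and wellbeing and stress) will be analysed by fitting similar regression models".

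The Objectives section names school performance among the secondary objectives, so this outcome answers a stated question of the trial.

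**The concern.** A logistic model of a yes/no threshold does not analyse a continuous measure. The article states both the scale and the model for the same outcome, and they do not match. This is a conflict between two stated rules, not a detail left out of a condensed article.

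Three things are at stake.

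- **Which result answers the objective.** A points-type score and a threshold can give different answers. An effect among weaker or stronger pupils, away from the threshold, would move the first and hardly touch the second.
- **Timing.** Children are 10 to 14 at baseline and 12 to 16 at the two-year follow-up (Discussion). A child aged 12 at follow-up reaches 15/16 some three to four years later. An unresolved definition would then be settled after the main results are known.
- **The trial's own aim.** The Discussion says the trial means to answer criticism of earlier trials of this programme over multiple testing and lack of pre-specification. Two definitions of one secondary outcome work against that aim.

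The declared outcome also names two quantities, a number of passes and a set of grades, without saying how they form one continuous measure.

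**Working it through.** **1. The sections side by side**

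| | Outcome measures | Main analysis |
|---|---|---|
| Quantity | Number of passes and grades | At least five GCSEs graded C or better |
| Scale | Continuous | Binary |
| Model | None given there | Two-level logistic |

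No other section gives a model for a continuous GCSE measure. The closing provision is limited to other outcomes. It follows directly on the GCSE analysis, and its examples are parenting, affective behaviour and wellbeing.

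The primary outcomes show how the article writes a two-scale analysis when it intends one. It declares the dichotomy as the outcome, and Main analysis adds a repeat on the original ordinal scale. Nothing comparable is said for GCSE.

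**2. The plan's own figure**

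The article states no sample size or power for GCSE. Its one sample size concerns the primary outcomes: "We will aim to recruit 378 families in each arm of the trial (756 families in total", for "at least 80% power at the 2.5% level (halved to account for our two primary outcomes".

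It reproduces for drinking, "12% difference in young people reporting having drunk alcohol (assuming a control group prevalence of 48"%, that is 48% against 36%. The inputs are two-sided alpha 0.025 (sidedness is not stated, so this is an assumption), 80% power and a continuity correction (also an assumption):

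- Young people per arm: 337
- Design effect: 1 + (1.25 − 1) × 0.2 = 1.05, and 337 × 1.05 = 353.9
- Families: 353.9 / 1.25 = 283.1
- Allowing for 25% loss: 283.1 / 0.75 = 377.4, rounded up to 378

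This neither supports nor weakens the GCSE point. It only supplies an effective sample size for step 4.

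**3. Information kept by a threshold (illustration)**

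Assume a normally distributed score and an intervention effect that is a pure location shift. Let p be the control proportion reaching the threshold and c the matching normal cut-point. The efficiency of the binary analysis relative to the continuous one is φ(c)² / [p(1 − p)].

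- p = 0.5: 0.159 / 0.25 = 0.637
- p = 0.3: 0.3477² / 0.21 = 0.576

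**4. What that would mean at this trial's size (illustration)**

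Effective young people per arm with 25% loss: 378 × 0.75 × 1.25 / 1.05 = 337.5. With an assumed two-sided alpha of 0.05, the shift giving 80% power on the continuous score is (1.960 + 0.842) × √(2 / 337.5) = 0.216 SD. The same shift analysed at the threshold gives:

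| Control proportion at threshold | Relative efficiency | Power, binary | Sample ratio (1/efficiency) |
|---|---|---|---|
| 30% | 0.576 | 58% | 1.74 |
| 40% | 0.622 | 60% | 1.61 |
| 50% | 0.637 | 61% | 1.57 |
| 60% | 0.622 | 59% | 1.61 |
| 70% | 0.576 | 55% | 1.74 |
| 80% | 0.490 | 47% | 2.04 |

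If linkage were complete (378 × 1.25 / 1.05 = 450 per arm, shift 0.187 SD), the powers are almost the same, 47% to 61%.

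**The case against.** The strongest reply is that this is a condensed article. The Sub-group & interim analysis section refers to a statistical analysis plan, which is not shown and may contain a continuous GCSE analysis. The general provision for other outcomes gives its examples as a non-exhaustive list, so a grade score might be argued to fall under it. The analysis section itself names a single attainment model with threshold, clustering and timing fixed. This is one of seven secondary outcomes, and an attainment threshold is a legitimate measure of school performance.

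Much of this stands, and it rules out some stronger readings.

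- A reader might infer that the declared outcome will never be tested. The article supports only that no such analysis is stated in it.
- A reader might infer that most of the grade information is thrown away. Even under the illustrative assumptions, 58% to 64% is kept at pass rates of 30% to 50%. It falls just below half only at 80%.
- A reader might take a loss of power as established. It rests on an assumed normal shift, whereas a count of passes with ordinal grades is bounded and discrete. The article claims no power for GCSE.
- A reader might infer that two rival analyses are on offer for later choice. Only one is written down. The conflict lies between it and the outcome's definition.

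The reply does not remove the mismatch. An unseen plan can excuse silence, but here the article states both scale and model, and a plan consistent with one section would contradict the other. The word 'other' in the general provision most naturally excludes an outcome whose analysis has just been given.

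**Conclusion.** The point holds as an inconsistency that should be corrected. The definition of GCSE performance and its only stated attainment analysis are on different scales, and the declared continuous outcome has no stated analysis in this article. That conclusion rests on the text alone and needs no power argument.

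The practical size cannot be fixed from the document. The efficiency figures of about 64% and 58%, and the fall from 80% power to between 47% and 61%, are illustrations under a normal score, a pure location shift and an assumed alpha of 0.05. The loss would be smaller if the effect were concentrated at the threshold. The primary outcomes, their analysis and the 378 families per arm are untouched.

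**What to change.** Settle one definition before the linked data are obtained.

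- **Preferred:** in Main analysis, name one continuous GCSE score, state how number of passes and grades are combined, and analyse it with a two-level linear model adjusted for the balancing variables and area. Keep the threshold of five GCSEs at C or better as a supplementary binary analysis.
- **Alternative:** if the threshold is the intended outcome, change Outcome measures so that GCSE performance is declared as binary.

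The cost is wording and, under the preferred option, one further model. A continuous score needs grade-level records. Outcome measures already presumes these, but the article does not list the fields that linkage will return, so their availability should be confirmed when the score is defined.
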